### Objectives

This pilot study was designed to lay the groundwork for a larger RCT using the MMP and building an evidence base to support broader dissemination of an effective, low-cost, highly scalable program. This pilot study has 3 primary aims.

#### Feasibility

This aim focused on assessing the practicality and reception of the intervention and research procedures among preschoolers, teachers, parents, and administrators, including evaluation of the acceptability of data collection methods, such as physiological, behavioral, qualitative, and survey measures. In this study, we draw from the work of Bowen et al [31] and Teresi et al [32], who outline facets of feasibility studies, including factors such as acceptability, implementation, and practicality (among others). These factors may be assessed by consenting to be part of a study, retention, satisfaction, and participation in activities.

#### Effects on Mechanisms and Outcomes

This aim focused on investigating how the implementation of the MMP influences self-regulatory capacities, SEL skills, problem behaviors, and prosocial behaviors, as well as identifying underlying physiological mechanisms of program effects at the midpoint, postintervention time point, and 2-month follow-up. Physiological data were collected after each MMP component, allowing for the evaluation of the effects of sequential implementation on physiological responses.

#### Teacher Effects

This aim focused on evaluating how exposure to MMPs affects teachers’ stress responses due to physiological attunement with children and classroom dynamics, which may subsequently enhance child outcomes.

## Methods

### Setting

Two sites, including 1 community-based site (2 classrooms) and 1 university-based site (1 classroom), participated in the study. These sites were chosen because they serve families from the local community, creating a more heterogeneous sample of children as opposed to focusing on disadvantaged or advantaged populations. Site 1 (community-based preschool program Head Start) had 8 active preschool classrooms, and site 2 (university-based preschool) had 3 active preschool classrooms. Site 1 receives federal funding to provide early childhood education for children from families living below federal poverty guidelines or facing other stressors such as homelessness or disability. Of the enrolled families, 90% were low-income families and 14% received public assistance [33]. Enrollment was determined by need. According to a county-level report for all Head Start sites in the broader study area, approximately 11% of children faced homelessness; 14% were referred for developmental disability or special education; and 32% received Supplemental Nutrition Assistance Program benefits. By comparison, an estimated 13% of the United States receives these benefits (Economic Research Service [34]). Site 2 uses an enrollment model that provides a diverse group of children and families. Using a stratified enrollment model, 25% of enrolled children were children of faculty members, support staff, university students (both undergraduate and graduate), and community families. Approximately 20% to 30% of the children enrolled came from low-income homes (supported by Child Care Assistance Program subsidy vouchers, a grant supporting childcare needs of low-income undergraduate student parents, and a sliding fee scale).

### Participants

A total of 40 participants were enrolled in the RCT part of the study. Participants included 32 preschool children aged 3 to 5 (mean 4.4, SD 0.64) years: 17 (53%) female, 11 (34%) Black, and 4 (12%) Hispanic. Demographics of children were based on parent reports unless those data were missing (n=3, 9%), in which case teacher-reported values were used. In total, 69% (22/32) of the children received the intervention immediately, and 31% (10/32) were assigned to the waitlist control group. Of the 40 participants enrolled across the 3 classrooms, 8 were female teachers with a mean age of 37.9 (SD 11.47) years: 3 (38%) were Black and 4 (50%) were White. A total of 29 parents with a mean age of 33.6 (SD 6.75) years completed the demographic questions: 23 (79%) female, 12 (41%) Black, and 2 (7%) Hispanic. Baseline demographics by intervention group for children and parents are presented in Tables 1 and 2.

**Table 1 table1:** Demographic characteristics of children (N=32).

Characteristics		Full sample	Intervention (n=22)	Control (n=10)
Age (y), mean (SD)		4.4 (0.64)	4.6 (0.50)	3.9 (0.72)
**Sex n (%)**				
	Male	12 (55)	—^a^	—
	Female	17 (53)	10 (45)	7 (70)
**Ethnicity, n (%)**				
	Hispanic or Latinx	—	—	—
	Not Hispanic or Latinx	28 (88)	21 (95)	7 (70)
**Race, n (%)**				
	Asian, Native Hawaiian, or Other Pacific Islander	6 (19)	5 (23)	—
	Black or African American	11 (34)	6 (27)	5 (50)
	White	15 (47)	11 (50)	4 (40)
**Language, n (%)**				
	Native English speaker	20 (62)	13 (59)	7 (70)
**Disability, n (%)**				
	None	27 (84)	17 (77)	10 (100)
	One or more disabilities	5 (16)	5 (23)	0 (0)

^a^Samples sizes of <5 participants.

**Table 2 table2:** Demographic characteristics of parents (N=29).

Characteristics			Full sample		Intervention (n=19)		Control (n=10)
Age (y), mean (SD)			33.6 (6.75)		34.8 (5.64)		30.9 (8.36)
Number of children, mean (SD)			2.1 (1.11)		2.0 (0.77)		2.4 (1.57)
**Sex, n (%)**							
	Male	6 (21)		6 (32)		—^a^	
	Female	23 (79)		13 (68)		10 (100)	
**Ethnicity, n (%)**							
	Hispanic or Latinx	—		—		—	
	Not Hispanic or Latinx	27 (93)		19 (100)		8 (80)	
**Race, n (%)**							
	Asian, Native Hawaiian, Other Pacific Islander	—		—		—	
	Black or African American	12 (41)		5 (26)		7 (70)	
	White	13 (45)		10 (53)		—	
**Education level, n (%)**							
	High school degree or GED^b^	9 (31)		5 (26)		—	
	Some college but no degree	6 (21)		—		—	
	Associate or bachelor degree	7 (24)		—		—	
	Graduate degree	7 (24)		7 (37)		—	
**Marital status, n (%)**							
	Single, living alone	6 (21)		—		—	
	Living with a romantic partner	—		—		—	
	Married	16 (55)		14 (74)		—	
	Separated or divorced	—		—		—	
**Employment status, n (%)**							
	Employed for wages or self-employed	23 (79)		13 (68)		10 (100)	
	Unemployed	6 (21)		6 (32)		—	
**Income range (US $), n (%)**							
	≤$26,000	8 (28)		6 (32)		—	
	$27,000 to $49,000	12 (41)		5 (26)		7 (70)	
	≥$50,000	7 (24)		7 (37)		—	

^a^Samples sizes of <5 participants, except for reported missingness.

^b^GED: General Educational Development.

### Procedures

This pilot study consisted of 8 formative focus groups with administrators and teachers who aimed to inform modifications to the study design before data collection and implementation. The RCT took place from January 2024 through August 2024 and consisted of multiple components (detailed below).

#### Formative Interviews and Focus Groups

In fall 2023, 6 focus groups were conducted with 33 teachers and 2 focus groups were conducted with 5 administrators. These formative focus groups were conducted at 3 Head Start locations and the university preschool to gauge teacher and administrator interest in participating in research studies and a proposed intervention study. All 33 teachers expressed positive sentiments about the program being implemented in classrooms; however, because this was a pilot study, we could only implement the program in 3 classrooms across 2 sites. Classrooms were selected based on the children served (those aged 3 to 5 years), teacher buy-in, and administrator feedback on the feasibility of implementation (eg, full-day classrooms vs half-day classrooms). The future full-scale RCT will randomize classrooms to conditions. The research team followed up with teachers in 3 identified classrooms and confirmed their willingness to participate in the research study before classroom selection was finalized.

#### Randomization Procedures

At site 1, a total of 2 classrooms were randomly assigned to receive the 16-week intervention or serve as the waitlist control group. Because randomization was only needed for 2 classrooms at site 1, we used a manual procedure by writing classroom numbers on pieces of paper, which were then folded and mixed, and one was drawn to assign the intervention group. The one classroom at site 2 was assigned to receive the 16-week intervention. A 2:1 ratio between the intervention and control groups was chosen to maximize the number of children receiving the intervention while maintaining a comparison group for evaluating the effectiveness of the program.

#### The Mindful Movement Program

The MMP combined movement practices (Mission2Move [35]) and positive behavioral intervention and supports (PBIS; Calm Caterpillar [36]) into one progressive program, referred to as M2M-CC (Mission2Move and Calm Caterpillar) for short. M2M-CC integrated evidence-based movement (Z-Health [37]) and meditation (Mindful Schools [38,39]) strategies. It was an SEL program that provided a mindful movement curriculum and tools to support classrooms and child development. M2M-CC practices included (1) neural-based drills, (2) aerobic activity, (3) breathwork and guided meditation, and (4) “feelings circle” or reflective practices. Positive behavioral intervention occurred with the use of visual and tactile aids, and support was provided through classroom or home kits that children, parents, and teachers could use in times when children needed assistance in regulating their emotions and behaviors. The movement (neural-based drills and aerobic activity) and mindfulness (breathwork and guided meditation, as well as reflective practices and “feelings circle”) practices worked in conjunction with each other to teach children how physical health is tied to social-emotional well-being and goal attainment [40]. Teachers and parents received a calm corner kit (classroom or home kits) near the end of the program to help children practice self-regulation techniques at home and in the classroom when direct instruction was not occurring.

#### Program Implementation

For the study, the program was delivered twice per week in classrooms receiving the intervention. One weekly session was a 15-minute mindful movement class and the other session was a 5- to 7-minute refresher or booster class. These classes were taught over 16 weeks (immediate intervention group) and 8 weeks (waitlist control). Study implementers were trained and supported by the MMP developer, one person led the implementation of the program to create consistency across sites, and an established curriculum was used to maintain standardization of the program. Before programming began, teachers received professional development training. During programming, teachers were present for direct instruction by study implementers so that they could learn the MMPs for use outside of planned programming and booster sessions each week and for future classroom implementation.

A 4-part sequence of program components was administered over time. First, children warmed up with “neural-based drills.” Drills used specific movements to train the nervous system in how body parts were supposed to move. These increased children’s body awareness in movement, location, and action (ie, proprioception). Neural drills included movements such as hip circles or ankle tilts. In addition to neural drills, children were led in aerobic movement–focused activities (eg, dance and running in place). Second, children learned a variety of “simple breathing practices” that used different techniques for varied benefits. For example, children learned hand breathing—inhaling and tracing up a finger, then exhaling and tracing down a finger—to support self-calming. Third, children engaged in a reflective practice known as “feeling circles,” where they talked about the meaning of different feelings and shared when they experienced the feeling. We used a “talking stick” approach whereby each child had the opportunity to share and be heard when they held the stick. Finally, classrooms and parents were provided a kit of tools for creating a calming corner as another component of PBIS to reinforce skills taught in the program.

As presented in Table 3 (based on a 15-minute mindful movement class), mindfulness program components were sequentially introduced every 4 weeks after the first component. For example, during a 16-week implementation, components were added every 4 weeks (weeks 1-4, 5-8, 9-12, and 13-16). In an 8-week-long administration, program components were added every 2 weeks. Movement was first introduced, followed by breathwork and meditation, then feeling circles or reflection, and finally the calm corner (PBIS). This allowed for assessing program component effects on physiological (ie, respiratory sinus arrhythmia and vagal efficiency) and SEL mechanisms.

**Table 3 table3:** Programming component description, impact, and implementation details.

Component	Description		Hypothesized impact	Timing		Weeks		Modality		Location		Method	
Neural drills	Activate the brain through specific body movements (eg, hip and arm circles)		Learn body awareness and inhibitory control	5 min		1-16		Movement		School		Direct instruction	
Aerobic activities	Elevate heart rate via different activities and movement sequences	Reduce overall stress and cortisol			10 min		1-16		Movement		School		Direct instruction
Breathwork and meditation	Practice breathing techniques (eg, hand, belly, lion’s breath, and body scan meditation)	Practice control over emotions			2-3 min		5-16		Mindfulness		School		Direct instruction
Feelings circles	Label feelings and share personal examples with the circle and emotion recognition	Practice reflection and learn empathy and interpersonal connection			2-3 min		9-16		Mindful		School		Direct instruction
Calming corner	Down-regulation strategies for children included a classroom kit and a home kit for parents, a quiet space with reduced stimuli, visual aids for self-calming, and tactile weighted toy for soothing and counting	Practice self-calming skills; removed from environmental stimuli (eg, sounds, people)			Varies		13 to ≥16		Positive behavioral intervention and supports		School and home		Child and adult self- guided

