#### Waitlist Control Procedures

For consistency of exposure to research team personnel, both the immediate intervention and waitlist classrooms were visited by the implementation team twice weekly for 20 minutes per week. For the waitlist classroom, implementers interacted with children during typical classroom activities (eg, reading and playing with sensory tables).

Following the 16 weeks of programming and postassessment time point, the waitlist group received 8 weeks of the MMP with each program component sequentially added every 2 weeks. This condition allowed for testing of shorter program dosage effects than longer ones.

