#### Data Collection Timeline

Data were collected at 4 time points: baseline (preintervention; all classrooms), midintervention time point (8 weeks into programming; all classrooms), postintervention time point (immediately following the 16-week intervention or waitlist period; all classrooms), and 2-month follow-up (2 months after the intervention; 1 intervention classroom). In the waitlist control group, the postintervention time point also served as their second baseline and the 2-month follow-up served as their postintervention time point (immediately after the 8-week intervention). The data collection time points are illustrated in Figure 1 for the intervention (black) and waitlist control (gray) groups. At each time point, survey data were collected electronically (in person or online) or via paper and pencil, whichever was feasible and preferred by participants. Behavioral assessments were administered at all time points except for the midintervention time point.

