##### Hormone Measurements

Hair was collected to measure cortisol, testosterone, and dehydroepiandrosterone (DHEA) levels to capture chronic stress and threat-challenge exposure. Cortisol, a hormone secreted by the HPA axis, is known to rise in response to stress [57]. Testosterone, produced by the HPG axis, also increases in response to challenging situations [58,59]. DHEA is closely linked to both cortisol and testosterone and is needed to tease out the unique coupling effect. DHEA is produced adrenally in both the gonads and the brain. DHEA and its sulfated analog are the most abundant hormones in the body, and as an adrenal androgen, DHEA operates as an end-product of both HPA and HPG axes [60]. By examining the coupling of HPA and HPG axes activity, both independently and together, we can better predict the risk of negative health outcomes related to stress [61]. In addition, exploring HPA and HPG coupling broadens the understanding of stress from the traditional “fight-or-flight” response to a more nuanced “threat-challenge” framework, which can apply to a wider range of real-world stressors [58,62].

Hair samples were collected from both children and teachers who consented to participate in this component of the study. These samples were used to assess cortisol, DHEA, and testosterone levels, as hair is highly sensitive to hormonal changes. Hair sampling is more feasible than saliva collection in preschool-aged children, and hormone measurement is more reliable in hair than fingernail clippings. Hair samples were collected at 3 time points: preintervention, postintervention, and 2-month follow-up time points. A 1-cm section of hair reflects approximately 1 month of growth. Therefore, with hair lengths of several centimeters, we were able to assess the change of time in hormonal activity, with the closest hair to the scalp representing the most recent hormone accumulation [63,64].

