**Self-report**				
	Sociodemographic	Age, sex, race or ethnicity, highest level of education achieved, household income, marital status, employment status, number of kids, and teachers’ role^b^	Parent and teacher	Before intervention
	Stress level	Perceived Stress Scale	Parent and teacher	Before intervention, after intervention, and follow-up
	Teachers’ changes	Teacher SEL^c^ Beliefs Scale Mindfulness in Teaching Scale	Teacher	Before intervention, after intervention, and follow-up

^a^These were also administered at the midintervention time point.

^b^Data collected only from teachers at follow-up.

^c^SEL: social-emotional learning.

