## Discussion

### Program Outcomes

The study investigates the effect of an MMP on preschool children’s social-emotional, behavioral, and cognitive outcomes, including effects on acute and chronic stress. A mixed methods approach was used, integrating quantitative, qualitative, and physiological data. The study addresses several notable gaps in the literature, including determining MMP effects on a sociodemographically diverse population of preschoolers, identifying differential responses by program component (eg, movement alone and movement plus breathing), and exploring underlying physiological and social-emotional mechanisms of intervention responsivity. Taking this approach will further enrich our understanding of the potential mechanisms and efficacy of mindfulness-based interventions.

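### The staggered roll-out cannot give component effects on SEL, and for HRV it gives only change over cumulative, sequential addition of components

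*Protocol article*

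**What the plan says.** Program Implementation describes the roll-out: "during a 16-week implementation, components were added every 4 weeks (weeks 1-4, 5-8, 9-12, and 13-16"). The order is fixed: "Movement was first introduced, followed by breathwork and meditation, then feeling circles or reflection, and finally the calm corner (PBIS"). Table 3 shows that nothing is withdrawn. Neural drills and aerobic activities run over weeks 1-16, breathwork over 5-16, feelings circles over 9-16, and the calming corner from week 13. The section then concludes: "This allowed for assessing program component effects on physiological (ie, respiratory sinus arrhythmia and vagal efficiency) and SEL mechanisms". Program Outcomes in the Discussion names among the gaps addressed "identifying differential responses by program component (eg, movement alone and movement plus breathing").

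The measurement schedule is given elsewhere:

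- **Scales.** Table 4 lists the Children's Behavior Questionnaire, the Strengths and Difficulties Questionnaire, the Student-Teacher Relationship Scale and the expulsion risk measure before intervention, after it and at follow-up. Footnote a, attached to the open-ended questions only, adds: "These were also administered at the midintervention time point".
- **Tasks.** Data Collection Timeline: "Behavioral assessments were administered at all time points except for the midintervention time point".
- **HRV.** HRV Measurement places recordings before the programme, at 4-week intervals tied to each new module, after it, and at follow-up.
- **Hair.** "Hair samples were collected at 3 time points: preintervention, postintervention, and 2-month follow-up time points".

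After the post-assessment, "the waitlist group received 8 weeks of the MMP with each program component sequentially added every 2 weeks".

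**The concern.** To credit a change to one component, the outcome must be measured on both sides of that component's introduction, and nothing else may change at the same time. The SEL scales and tasks fail the first condition. The within-classroom HRV series fails the second.

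Differences between 4-week HRV steps could be reported as effects of breathwork or feelings circles when they also contain maturation, order and accumulated exposure. A component effect on SEL could be claimed when the data hold only a whole-programme change. The pilot is meant to prepare a full-scale trial that will look at responsiveness to components, so a mislabelled step could affect which components are carried forward.

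**Working it through.** No figure in the article is at issue. The check is whether each component effect is estimable from the stated schedule.

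**Inputs.** Start weeks from Table 3: neural drills (N) 1, aerobic (A) 1, breathwork (B) 5, feelings circles (F) 9, calming corner (C) 13, all kept to the end. Scale and task occasions: weeks 0 and 16 (Table 4, Data Collection Timeline). HRV occasions: weeks 0, 4, 8, 12 and 16, an assumption of one per module. Each component is coded off or on at each occasion. An effect is estimable if adding its contrast to the design matrix leaves the rank unchanged.

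**SEL scales and tasks.** At week 0 all five indicators are 0; at week 16 all five are 1. Even with a concurrent control and period effects, the only usable contrast is

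change(intervention) − change(waitlist) = N + A + B + F + C.

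That is one equation for five unknowns (rank 4 of 8 columns). The sum is estimable and no single term is. The follow-up adds no step at which a component enters. Had the scales also been taken at week 8, the two contrasts would be N + A + B (weeks 0-8) and F + C (weeks 8-16), which still gives no single component.

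**HRV, 16-week classrooms alone.** N and A enter together, so write M = N + A; they are never separable. With a linear time trend of g per week, the four successive differences are

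M + 4g, B + 4g, F + 4g, C + 4g.

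Four equations, five unknowns: no step is estimable. Free period effects give the same answer. Only with no time effect at all do the differences equal M, B, F and C.

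**HRV with a concurrent waitlist series.** If the waitlist class was recorded in the same weeks, the between-group differences in change are M, B, F and C, estimable if there is no carry-over and no effect of accumulating exposure. Adding a term of d per week of exposure turns them into M + 4d, B + 4d, F + 4d, C + 4d, and no step is estimable.

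**HRV using the waitlist's own 2-week roll-out.** With equal step effects and a common linear trend, that class gives M + 2g, B + 2g, F + 2g, C + 2g. Subtracting, (B + 4g) − (B + 2g) = 2g, so g is identified and all four steps follow (rank 7 of 7). If each group has its own slope, no step is estimable (rank 7 of 8).

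| Data | Model | Estimable |
|---|---|---|
| Scales, tasks (weeks 0, 16) | control + period effects | whole programme only |
| HRV | 16-week classrooms, any time trend | no step |
| HRV | concurrent control + period effects | M, B, F, C |
| HRV | the same + weeks of exposure | no step |
| HRV | waitlist 2-week roll-out, common linear trend | M, B, F, C |
| HRV | waitlist 2-week roll-out, separate slopes | no step |

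**The case against.** The best reply is that the article claims less than this suggests. It speaks of assessing component effects, not isolating them. The aim on mechanisms and outcomes refers only to the effects of sequential implementation on physiological responses, the Discussion's own example is a cumulative contrast, and the Conclusions leave responsiveness to components to an adequately powered trial. That stands as a reason to call this a correction of claims. It does not rescue the SEL claim, because no analysis can recover scale values that were not taken.

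A reader might infer several stronger conclusions that the documents do not support:

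- **No hormone information exists between weeks 0 and 16.** Hair was sampled only at the ends of that period, but Hormone Measurements says about 1 cm of hair reflects a month and that longer hair shows change over time. A post-intervention sample of about 4 cm would cover roughly four monthly windows. Achieved lengths are not given, and the order and time confounding remains.
- **No behaviour data exist in that period.** Session logs record engagement and disruptiveness. They are implementation measures, not the SEL scales.
- **Component and period are perfectly collinear across the whole design.** This holds within the 16-week classrooms. The waitlist's 2-week steps break it under the assumptions shown above.
- **No waitlist HRV was recorded during weeks 1-16.** The text is silent rather than negative, and the figure of time points is not available.
- **Mechanism can never be placed before outcome.** That applies to SEL as a mechanism. HRV during the programme does precede the week-16 outcomes.

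The Data Collection Timeline also says that survey data were collected at each time point, and the aim on mechanisms mentions the midpoint. Neither names a scale taken then, and Table 4 is the specific schedule.

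**Conclusion.** The component claim is wrong as written for SEL. With no SEL or behaviour scale and no behavioural task between baseline and week 16, only the combined effect of all five components is estimable, with or without the control classroom. This follows from the stated schedule and needs no distributional assumption.

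For HRV the problem is confounding, not missing data. Neural drills and aerobic activity are inseparable under every model examined. Within the 16-week classrooms, any time trend leaves no step estimable. Comparison with the waitlist class can separate the steps only if HRV was recorded there at matching steps, and only under strong assumptions: no carry-over or cumulative-exposure effect for the concurrent comparison, or equal step effects with a common linear trend for the 2-week roll-out. These are statements about identifiability; with three classrooms, any such estimate would also be weak evidence. The HRV result assumes one recording per module at weeks 4, 8, 12 and 16.

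**What to change.** 1. In Program Implementation, remove SEL from the component-effect sentence. Limit SEL scale and task analyses to the whole programme: baseline to week 16, and follow-up.
2. In Program Implementation and Program Outcomes, restate the physiology claim as change over cumulative, sequential addition of components, in line with the aim on mechanisms and outcomes.
3. State whether HRV was recorded in the waitlist class during weeks 1-16 and at its own 2-week steps. If it exists for the same weeks, analyse the intervention-minus-waitlist difference in change at each step, with the assumptions stated. If not, report the steps descriptively.
4. Segmental hair hormone values may be used within weeks 0-16 under the same caution.
5. Reconcile the aim on mechanisms and the Data Collection Timeline with Table 4 on what was measured at the midpoint.

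The cost is wording and a shorter list of analyses; no new data are needed. The downside is that the component question moves to the full trial.
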